## Background

Coronary heart disease (CHD) is the leading cause of mortality and morbidity in the world [1]. In 2012 CHD accounted for approximately 7.4 million lives, an increase of 23 % (1.4 million) from CHD deaths in 2000 [1]. Patients at highest risk of premature death, myocardial infarction and re-hospitalization are those with known CHD [2]. Consequently international guidelines strongly advocate proven secondary prevention strategies such evidence-based pharmacological therapy, cardiovascular risk factor optimization, cardiac rehabilitation and adherence to diet and physical activity recommendations [3].

Cardiac rehabilitation provides a comprehensive secondary prevention framework based on extensive scientific evidence. A recent Cochrane review revealed cardiac rehabilitation was associated with a 13 % decrease in all-cause mortality and a 26 % decrease in cardiovascular mortality [4]. This result is consistent with several other meta-analyses [5–7].

However, there is poor translation of scientific evidence into clinical practice. Cardiac rehabilitation services are underutilized as highlighted by low referral rates and even lower completion rates [8–12]. In addition, utilization of recommended pharmacological therapy and compliance with dietary and physical activity guidelines is suboptimal [13–16]. Lastly, outpatient cardiac rehabilitation often starts weeks to months after the index event, even with the utilization of new technology [17]. This delay creates a missed opportunity to immediately reinforce the importance of physical activity and lifestyle changes. Furthermore, the delay in cardiac rehabilitation has been associated with delayed resumption of work [18].

The drawbacks of conventional cardiac rehabilitation have resulted in the development of innovative models of care. In the seminal paper by Vale et al, regular personal coaching via telephone has been shown to be effective in reducing total cholesterol levels and other cardiovascular risk factors [19]. Systematic reviews and meta-analyses have shown telehealth interventions for secondary prevention, limited to telephone calls, internet and videoconferencing technologies, offer an effective alternative model of secondary prevention care [20, 21].

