### Intervention

The smartphone-based secondary prevention program will be delivered over 8 weeks starting at time of discharge from hospital through a smartphone application (app). Participants in the smartphone intervention cohort will download the intervention application (“app”) into their smartphone. They will then receive education on how to use the app. The SSPP is a multi-faceted intervention with particular emphasis on early physical activity. The app provides a platform to deliver a comprehensive secondary prevention program (Fig. 2). Participants can log off the app at any time effectively not undertaking the SSPP. The different components of the SSPP are discussed in detail below.

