### Standard care

Regardless of the treatment arm, all patients will receive standard of care treatment post-ACS. This includes inpatient cardiology review, pre-discharge planning, formal communication with general practitioner through a discharge summary letter, referral to cardiac rehabilitation, promotion of self care and a chest pain action plan.

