#### Secondary outcomes

In general, all secondary outcomes will be measured at baseline and at 8-week follow-up. Table 2 summarises the secondary outcomes of our study.

**Table 2 Tab2:** Primary and secondary endpoints

Primary Outcome • Change in six-minute walk test distance
Secondary Outcomes • Fasting lipid levels (TC, LDL-C, HDL-C, TG) • Fasting glucose • Resting blood pressure • Weight and body mass index • Waist circumference • Smoking status (self-reported) • Uptake, Adherence and Completion of cardiac rehabilitation • Major adverse cardiovascular events • Cardiovascular hospital re-admissions • Depression assessment (CDS and DS-SF questionnaires) • Anxiety assessment (HADS questionnaire) • Quality of life assessment (SF-36 questionnaire) • Health outcome assessment (EQ-5D questionnaire) • Time to return to work • Secondary prevention pharmacotherapy use (self-reported) • Six minute walk test distance at 8-weeks

Body mass index will be derived from the weight (kg) divided by height (m) squared. Waist circumference will be measured using an anthropometric tape placed around the participant’s waist at the level of the umbilicus. An electronic sphygmomanometer with pulse oximetry will be used to assess the systolic and diastolic blood pressure as well as resting heart rate.

Fasting glucose and cholesterol levels will be measured after 12 h of fasting. It will be analyzed at the pathology department of the corresponding hospital in standard fashion.

Smoking status, medication compliance and current medication list will be assessed via self-reporting at the 8-week assessment. The date the participant returns to work, if applicable, will also be collected to assess the time to resumption of work after acute coronary syndromes.

Uptake, adherence and completion of a cardiac rehabilitation program will be assessed. Uptake is defined as attending at least one exercise session for traditional cardiac rehabilitation or uploading 1 day’s physical activity in the SSPP. Adherence is defined as attending 4 weeks’ or uploading 12-days of activity over 4 weeks of physical activity. Completion is defined as showing adherence to cardiac rehabilitation and attending the 8-week assessment session.

Major adverse cardiovascular events (MACE) will be recorded. MACE is defined as the composite of death, myocardial infarction, stroke and unplanned revascularization.

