## Discussion

This novel study aims to evaluate the impact of a smartphone based secondary prevention program on functional capacity of patients with acute coronary syndromes. The benefit of comprehensive secondary prevention programs incorporating physical activity is well recognised. Smartphone technology could hold the key to bridging the well documented gap between scientific evidence and clinical practice.

This randomised clinical trial also aims to build the scientific base supporting alternative models of secondary prevention care in patients post acute myocardial infarction. Of particular note, is the initiation of this program as soon as the patient is discharged from hospital post their index event. This is a crucial period of recovery and immediate initiation of smartphone based secondary prevention program may facilitate early physical activity and return to normal daily function, including resumption of work.

The primary endpoint aims to objectively assess improvement in physical activity through the use of the six-minute walk test. Near maximal exercise testing is safe in patients with uncomplicated myocardial infarction prior to discharge and thus early mobilisation should be encouraged [37, 38]. The superiority trial design is suitable to detect a minimal clinically important difference in 6-minute walk distance [31]. It is postulated the improvement will be due to earlier initiation of an exercise program and increase in uptake and adherence with cardiac rehabiliation.

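### Rehabilitation uptake, adherence and completion include an app-upload route open only to the intervention arm, so the between-arm difference is not a like-for-like effect on attendance

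*Protocol article*

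**What the plan says.** Table 2 of the protocol article lists "Uptake, Adherence and Completion of cardiac rehabilitation" among the secondary outcomes, and the text below it fixes the definitions:

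- **Uptake:** "Uptake is defined as attending at least one exercise session for traditional cardiac rehabilitation or uploading" a single day of activity. The second route is worded "uploading 1 day’s physical activity in the SSPP".
- **Adherence:** four weeks of attendance, or "uploading 12-days of activity over 4 weeks of physical activity".
- **Completion:** adherence plus attendance at the 8-week assessment, so it carries both routes forward.

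Two other sections determine who can use each route. Under Intervention, "Participants in the smartphone intervention cohort will download the intervention application"; nothing gives the app to controls. Under Standard care, "Regardless of the treatment arm, all patients will receive standard of care treatment post-ACS", and referral to cardiac rehabilitation is listed as part of that care.

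The Discussion then gives the outcome an explanatory role: "It is postulated the improvement will be due to earlier initiation of an exercise program and increase in uptake and adherence", the uptake and adherence in question being to cardiac rehabilitation. Under Statistical analysis, categorical variables are compared by Fisher's exact or chi-square tests, and treatment evaluation is by intention to treat.

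**The concern.** As worded, an intervention patient can qualify by attending sessions or by uploading from the app, while a control patient can qualify only by attending. The additional route is use of the randomised intervention itself. If the app left attendance at traditional rehabilitation unchanged, the rule could still produce a difference in favour of the intervention arm, and the test could declare it significant.

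Two conclusions are at stake. The result could be reported as increased uptake of cardiac rehabilitation, which is how the outcome is named in Table 2 and the abstract. It could also be cited as confirming the Discussion's explanation for a gain in walk distance. Neither follows from a measure that counts different behaviours in the two arms.

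Timing may add to the imbalance for adherence. The Background remarks that "outpatient cardiac rehabilitation often starts weeks to months after the index event", whereas the app programme starts at discharge. A patient whose sessions begin after week 4 cannot accumulate four weeks of attendance by the 8-week visit (4 + 4 = 8). The article gives no start times for the trial hospitals, so the size of this effect is unknown.

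**Working it through.** The plan states no expected rate, effect or power for these outcomes, so there is no figure of its own to reproduce. Its only design calculation concerns the six-minute walk test: 76 per group, with 100 per arm recruited to allow for 20% loss. Only the arm sizes are used here.

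**Inputs**
- p, the true proportion attending at least one traditional session, set equal in both arms. The illustrative value is 68%, the comparator uptake in a smartphone rehabilitation trial cited in the Background. That trial's definition of uptake is not given in the article.
- a, the proportion of intervention patients uploading at least one day. The article gives no value. The assumed range is 50% to 94%; the upper end is the smartphone-arm uptake in the same cited trial.
- 100 per arm, or 80 per arm after 20% loss (100 × 0.8); two-sided 5% test.

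**Reading 1: either route counts in the intervention arm.** With independent routes, intervention uptake is 1 − (1 − p)(1 − a) and control uptake is p.
- a = 50%: 1 − 0.32 × 0.50 = 0.84. Reported 84% vs 68%, +16 points.
- a = 94%: 1 − 0.32 × 0.06 = 0.981. Reported 98% vs 68%, +30 points.

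For a = 50% and 100 per arm, the chance of a significant result is found as follows:
- Pooled proportion 0.76; null standard error √(2 × 0.76 × 0.24 / 100) = 0.0604.
- Standard error under the alternative √((0.84 × 0.16 + 0.68 × 0.32) / 100) = 0.0593.
- (0.16 − 1.96 × 0.0604) / 0.0593 = 0.70, which gives about 76%.

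At 80 per arm the same case gives about 66%. At a = 94% the chance is close to 100% at either size. An upload proportion of about 53% is enough for an 80% chance at 100 per arm when p = 68%; with p = 50% it is about 39%, and with p = 30% about 28%.

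**Dependence between the routes.** Without independence, intervention uptake lies between max(p, a) and min(1, p + a). For p = 68% that is 68% to 100% at a = 50%, and 94% to 100% at a = 94%. With equal attendance the difference cannot be negative. It is zero only if every uploader also attends.

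**Reading 2: only uploads count in the intervention arm.** The difference is a − p: +26 points at 94% vs 68%, but −18 points at 50% vs 68%. The sign then depends on app use, not on attendance.

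**One common rule.** If traditional attendance is counted the same way in both arms and is truly equal, the expected difference is zero and the test rejects at about its nominal 5%.

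**The case against.** The strongest reply is that the app is offered as an alternative model of secondary prevention, so counting its use as participation is deliberate. Under intention to treat, the comparison remains a randomised contrast in engagement with whichever programme was offered, and starting at discharge is part of the intended benefit. That stands. A reader might infer that the comparison is no treatment effect at all, but that goes too far. It is an effect on a differently defined quantity.

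A reader might also infer that the intervention arm reaches nearly 100% uptake by construction. The article does not support this. The rule requires an upload, not possession of the app; participants may log off at any time; and no upload rate is stated. Under Reading 1, 95% uptake needs a = 1 − 0.05 / (1 − p), about 93%, 90% and 84% for p of 30%, 50% and 68%. Adherence, with its 12 upload days, is further from automatic.

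Nor can it be shown that 12 upload days is the easier bar. The article gives no session frequency for the four weeks of attendance.

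Displacement is another tempting inference. If attendance fell to 50% in the intervention arm while 90% uploaded (both hypothetical), independent routes would give 1 − 0.50 × 0.10 = 95% against 68%. The combined measure alone would not reveal the fall. But nothing in the article says displacement is expected, or that attendance will go unreported by arm.

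Finally, this is one of 16 secondary lines in Table 2. It is listed in the abstract but absent from the stated aim and hypotheses, and the Discussion offers its mechanism only as a postulate alongside earlier initiation. This limits the severity. It does not make the two arms' criteria comparable.

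**Conclusion.** The point holds as a secondary-outcome problem that should be fixed. Uptake, adherence and completion contain a qualifying route that one arm cannot use, so a between-arm difference measures programme engagement and cannot by itself show increased rehabilitation attendance or support the postulated mechanism.

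At equal true attendance of 68%, the either-route reading gives an apparent gain of about 16 to 30 points for upload proportions of 50% to 94%. These sizes are illustrative: they rest on a borrowed attendance rate, assumed upload rates and independent routes. The structural fault does not depend on those values. The article also leaves unclear whether both routes or only uploads count in the intervention arm, and on the second reading the direction is not fixed. The six-minute walk endpoint and its sample size are untouched.

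**What to change.** - Base the between-arm comparison of uptake and adherence, and of the completion built on adherence, on attendance at traditional cardiac rehabilitation. Record it in both arms with one rule and the same 8-week window.
- Report upload days separately and descriptively as SSPP engagement, within the intervention arm only.
- If a combined either-programme measure is kept, which is a legitimate choice, label it programme engagement, say which routes count in each arm, and do not cite it as evidence of increased rehabilitation uptake.

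The cost is a change of definition and the recording of session attendance in both arms by the existing 8-week assessment. The reported difference may be less favourable to the app, and an attendance-only comparison gives no credit to a patient who uses the app fully but attends no sessions. The separate engagement report covers that patient.

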### Statistical analysis

Statistical analyses will be performed using SPSS (IBM, USA). Baseline characteristics will be summarized using descriptive statistics. Continuous variables will be described as mean and standard deviation and be compared using Student’s *t* test. Categorical variables will be described as frequencies and percentages and compared using Fisher’s exact or chi-square tests as appropriate. Treatment evaluation will be performed on an intention to treat (ITT) analysis.

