### Eligibility and recruitment

Patient over the age of 18 with a diagnosis of an acute coronary syndrome and documented coronary artery disease on coronary angiography (coronary artery stenosis >50 %), who are treated either medically or with percutaneous coronary intervention will be eligible for inclusion. The other major inclusion criteria will be personal ownership of a smartphone.

Exclusion criteria include untreated ventricular tachycardia, severe heart failure, significant residual coronary artery disease requiring revascularization, treatment with coronary artery bypass surgery, coexisting disease with a life expectancy less than 1 year and/or significant exercise limitations for reasons other than CHD.

Recruitment will occur during hospital admission at six major university affiliated teaching hospitals in Victoria, Australia. All patients admitted with acute coronary syndromes will be screened and those meeting the entry criteria will be selected. Potential participants will receive study information and informed consent will be obtained.

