### Randomization and blinding

Eligible patients will be randomized in a 1:1 fashion to smartphone-based secondary prevention program or usual care through a computerized randomization program. Randomization will be stratified by study site and be overseen by the Centre of Cardiovascular Research and Education in Therapeutics at Monash University; an independent research body within the School of Public Health and Preventive Medicine at Monash University, Melbourne, Australia. Baseline assessment, including the 6-minute walk test, will occur prior to randomization. Assessors of the primary outcome are blind to treatment allocation; however participants are not blinded.

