#### Primary outcome

The primary outcome is change in six-minute walk distance that will be measured in standardized fashion [34]. The initial test will be undertaken prior to hospital discharge and this will be repeated at 8 weeks as an outpatient, without monitoring.

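### The only method named for continuous variables is an unadjusted t test, applied to a change score; ANCOVA on baseline distance and site would be at least as precise at almost no cost

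*Protocol article*

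**What the plan says.** All references are to the protocol article.

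- **Endpoint** (Primary outcome; also Abstract and Table 2): "The primary outcome is change in six-minute walk distance", from a test before discharge to one at 8 weeks. Table 2 also lists "Six minute walk test distance at 8-weeks" as a secondary outcome.
- **Method** (Statistical analysis): "Continuous variables will be described as mean and standard deviation and be compared using" Student's t test. Fisher's exact or chi-square tests are named for categorical variables. A separate sentence then says: "Treatment evaluation will be performed on an intention to treat (ITT) analysis". No covariate, regression model or site term appears anywhere in the article.
- **Baseline and design** (Randomization and blinding): "Baseline assessment, including the 6-minute walk test, will occur prior to randomization", and "Randomization will be stratified by study site". Six hospitals recruit (Eligibility and recruitment).
- **Size** (Sample size calculation): 76 per group for a 25 m difference, 80% power and 5% significance; 100 per arm recruited to allow for 20% loss. No SD is given.

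**The concern.** The design supplies two pieces of prognostic information before allocation: each patient's baseline walk distance and the site. The only stated method for a continuous outcome uses the first through simple subtraction and the second not at all.

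Subtracting baseline assumes that each extra metre walked at baseline predicts exactly one extra metre at 8 weeks. Here baseline is an in-hospital test soon after an acute coronary syndrome and follow-up is an outpatient test 8 weeks later, so there is no particular reason for the slope to be 1. If it is not, the change score is noisier than it need be, and part of any chance baseline difference between arms stays in the estimate. At stake is precision on the primary endpoint in a trial that expects to lose 20% of its patients.

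**Working it through.** **Inputs from the article.** Difference 25 m; 76 per arm; 80% power; 5% significance; 1:1 allocation; 20% loss; 100 per arm recruited.

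**Assumptions.** Two-sided test; the correlation r between baseline and 8-week distance, which is varied; equal SDs at both visits (relaxed in step 4).

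**1. The plan's own figure.** With no SD stated, 76 per arm cannot be reproduced independently, only inverted:

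SD = 25 / [(1.960 + 0.842) × √(2/76)] = 25 / (2.802 × 0.1622) ≈ 55.0 m (54.7 m with the noncentral t).

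Putting 55 m back in returns 76 per arm, which is consistent but circular. A one-sided test would imply 62.0 m. The loss allowance is adequate: 76/0.8 = 95, below the 100 recruited, and 100 × 0.8 leaves 80 per arm.

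**2. Variance comparison.** With common SD s at both visits:

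- Var(change) = 2s²(1 − r)
- Var(ANCOVA residual) = s²(1 − r²)
- Ratio ANCOVA/change = (1 + r)/2

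**3. Power, taking 55 m as the SD of change** (normal approximation). Example for r = 0.7: residual SD = 55 × √0.85 = 50.7 m; SE = 50.7 × 0.1622 = 8.22 m; 25/8.22 − 1.96 = 1.08; power = 86%.

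| r | variance ratio | residual SD (m) | power at 76/arm | n/arm for 80% | CI narrower by |
|---|---|---|---|---|---|
| change-score t test | 1 | 55.0 | 80% | 76 | – |
| 0.5 | 0.75 | 47.6 | 90% | 57 | 13% |
| 0.6 | 0.80 | 49.2 | 88% | 61 | 11% |
| 0.7 | 0.85 | 50.7 | 86% | 65 | 8% |
| 0.8 | 0.90 | 52.2 | 84% | 69 | 5% |
| 0.9 | 0.95 | 53.6 | 82% | 73 | 2.5% |

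**4. Unequal SDs.** In general, Var(change) − Var(ANCOVA) = (SD_baseline − r × SD_follow-up)². This is never negative. It is zero when SD_follow-up/SD_baseline = 1/r, that is 1.43 at r = 0.7 or 1.25 at r = 0.8. Take r = 0.7, SD_baseline = 1 and SD_follow-up = 1.2:

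- Var(change) = 1 + 1.44 − 2 × 0.7 × 1.2 = 0.760
- Var(ANCOVA) = 1.44 × (1 − 0.49) = 0.734
- Reduction = 0.026/0.760, about 3%, instead of 15% with equal SDs.

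**5. If 55 m is instead the SD of distance at one visit.** Power at 76 per arm, change score against ANCOVA: 66% v 84% (r = 0.3), 80% v 90% (0.5), 95% v 98% (0.7), about 100% for both (0.9). The direction is the same but the size differs.

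**6. Chance baseline imbalance.** Let D be the baseline difference between arms and β the regression slope of 8-week on baseline distance. The change-score estimate differs from the ANCOVA estimate by −(1 − β)D. With equal SDs β = r, so D = 20 m moves it by 10, 6 or 2 m at r = 0.5, 0.7 or 0.9. This is the same loss as in step 2, seen conditionally: 2s²(1 − r) − s²(1 − r²) = s²(1 − r)².

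**7. Site.** Leaving a stratification factor out usually makes the t test conservative. No between-site variance is given, so no figure can be attached.

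**The case against.** **The t-test sentence may describe only the baseline table.** It follows directly on the sentence about baseline characteristics, and treatment evaluation comes later with only intention to treat specified. On that reading the primary model is simply not given in a condensed article, and a full analysis plan may supply it. This stands as a limit on certainty. However, the sentence speaks of continuous variables without restriction, and no other method is offered for the primary outcome. The recommended sentence is useful on either reading.

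**A t test on a pre-specified change score is sound.** This stands. A reader might infer that the analysis is biased, ignores baseline or leaves the trial underpowered. The article does not support that: subtraction does use baseline, the estimate is unbiased over randomizations, and 80 retained per arm gives about 82% power at the implied SD.

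**The gain is assumption-driven.** This also stands. The article gives neither r nor an SD, and does not say whether its calculation concerns change or 8-week distance. At r = 0.9 the gain is about 2 percentage points of power.

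**The imbalance shift is not a second harm.** Correct: it is the precision loss again, and the confidence interval already reflects it.

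**Listing 8-week distance as well does not create two competing answers.** A reader might think it does, because unadjusted differences in change and in 8-week distance differ by exactly the baseline imbalance. But change is consistently the primary outcome, so it is clear which result decides. Removing the secondary outcome, or requiring site-adjusted models for binary outcomes, would be preference.

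**Conclusion.** The point holds as one of efficiency, not validity. The endpoint is fixed as a change score, the only named method for continuous variables is unadjusted, and both baseline distance and site are available before allocation. Apart from a few degrees of freedom, ANCOVA cannot be less precise than the change score, and the two tie only when the true slope is 1.

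If 55 m is the SD of change and SDs are equal at both visits, the gain runs from about 10 percentage points of power at r = 0.5 to about 2 at r = 0.9. It shrinks towards zero as the SD ratio approaches 1/r. A reader might also infer that intervals are too wide by a known amount because site is omitted; the article gives nothing from which to calculate that. Nothing here shows the planned sample size to be inadequate. The change is worth making because it costs so little.

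**What to change.** Before unblinding, state the primary analysis as ANCOVA of 8-week six-minute walk distance on treatment arm, baseline distance and study site, reporting the adjusted mean difference with its 95% CI. Using change as the response gives the identical treatment estimate, because only the baseline coefficient alters (β becomes β − 1), so the primary outcome need not be redefined. Use the same model for continuous secondary outcomes that have a baseline value. The 8-week distance may stay in Table 2, since under this model it yields the same treatment estimate as change.

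The cost is one sentence and six degrees of freedom (one for baseline, five for six sites) out of 2 × 76 − 2 = 150. No extra patients, visits or data are needed.
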